### 2.3. Eligibility Criteria

Participants for this study will be recreational adult dancers aged ≥ 18 years with a minimum of 6 months prior recreational dance experience at community dance schools. Eligible participants must demonstrate capacity for sustained moderate-intensity movement (60 min sessions) and good health with no severe musculoskeletal injuries within the past 2 weeks or intense medical conditions preventing coordinated group movement. Participants must commit to attending at least 70% of sessions (minimum 8 of 12 weeks) and baseline and post-intervention assessments, and be fluent in Greek language (written/verbal).

Exclusion criteria include: (1) active engagement in concurrent mindfulness-based or somatic-movement practices (yoga, Pilates, tai-chi, MBSR programs, etc.), which share theoretical overlap with the intervention’s mindfulness and embodied awareness components and could confound results; (2) severe psychiatric symptomatology requiring clinical psychiatric intervention (hospitalization, crisis stabilization, active suicidality). However, individuals with stable, treated psychiatric conditions are eligible, provided they have been stable on their current medication for a minimum of 6 months and have medical clearance from their treating clinician confirming appropriateness for moderate-intensity physical activity; (3) active substance abuse or dependence (current or within the past 12 months); (4) significant uncorrected hearing or vision impairment affecting the ability to participate in group dance and receive verbal or visual instructions; (5) current pregnancy; (6) acute physical contraindication to movement, including intense musculoskeletal injury occurring within 2 weeks prior to enrollment, severe infection, or uncontrolled cardiovascular event.

Individuals with injuries, mild to moderate, well-controlled chronic medical conditions (e.g., diabetes, hypertension, asthma, arthritis) or stable chronic psychological conditions are not exclusionary if participants provide written medical clearance from their treating physician/clinician confirming capacity for sustained moderate-intensity movement (90–100 min sessions) and documenting any activity modifications required. Severe or poorly controlled chronic conditions are exclusionary and require individual assessment by the principal investigator in consultation with the participant’s clinician.

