During preliminary telephone or in-person screening, trained site coordinators conduct structured interviews assessing adherence to inclusion and exclusion criteria. Prospective participants receive a comprehensive eligibility information sheet listing all criteria in accessible language and are invited to self-identify any exclusions or concerns. Those meeting preliminary eligibility criteria (age ≥ 18, minimum 6 months recreational dance experience, availability to attend ≥70% of sessions, Greek language fluency) proceed to formal baseline assessment. Site coordinators maintain a screening log documenting all preliminary screenings, including numbers screened, numbers excluded at each stage, and reasons for exclusion, to enable identification of potential selection bias.

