Participants proceed to formal baseline assessment (T0), which includes informed consent and administration of quantitative outcome measures (SWLS, DASS-21, MAAS, SHS, LIS; approximately 20–30 min). After completion of baseline assessment (T0), eligible participants are randomly allocated 2:1 (intervention: control) using computer-generated randomization with allocation concealment (administered by an independent data manager not involved in recruitment or assessment). Randomization is conducted via a secure, password-protected electronic system accessible only to the data manager, ensuring that recruitment staff and outcome assessors remain blind to allocation. Following randomization, intervention group participants receive full disclosure of the 12-week dance-mindfulness protocol and provide additional written informed consent confirming understanding of the intervention and commitment to attending the sessions.

Control group participants receive written guidelines regarding their usual recreational dance activities during the 12–week study period, including instructions to exclude concurrent mind–body practices (yoga, Pilates, tai-chi, MBSR programs, etc.). Control group participants are informed that they will have access to the full 12-week dance-mindfulness program at no cost after post-intervention assessment (T2, Week 12), providing equitable delayed intervention access.

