### 2.6. Intervention and Control Conditions

The intervention group will consist of participants who attend 12 weekly sessions (90–100 min each) structured across three phases: (1) Foundations (Weeks 1–4), (2) Embodied Exploration (Weeks 5–8), and (3) Expressive Integration (Weeks 9–12). Each session integrates eight standardized components (warm-up/breath grounding, technical dance work, conditioning, mindful break, rhythm/improvisation, choreographed sequences, cool-down/reflective integration, phenomenological journaling). Detailed component descriptions, facilitator language, and session structure are specified in Supplementary File S1 [27].

The control group will consist of participants who continue usual recreational dance activities (preferred modern dance and/or contemporary classes) for 12 weeks, excluding mind–body practices (e.g., yoga, Pilates, tai-chi) that share overlap with the intervention. Control participants do not receive mindfulness training, somatic cuing, or reflective journaling prompts. After post-intervention assessment (T2, Week 12), control participants are offered access to the full 12–week Dance-Mindfulness program at no cost (delayed intervention, ethical equity control).

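### The 12-week instruction to avoid outside mind-body practice is stated for the control arm only, and no recording of such practice is described in either arm

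*Protocol article*

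**What the plan says.** At entry the rule is common to both arms. Exclusion criterion 1 in Section 2.3 bars "active engagement in concurrent mindfulness-based or somatic-movement practices (yoga, Pilates, tai-chi, MBSR programs, etc", and the reason given is that these are practices "which share theoretical overlap with the intervention’s mindfulness and embodied awareness components and could confound results". Section 2.3 also says "Prospective participants receive a comprehensive eligibility information sheet listing all criteria in accessible language", so every candidate sees this criterion before enrolment.

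After randomization the text differs by arm. Under Section 2.4, controls get written guidelines for the 12 weeks, "including instructions to exclude concurrent mind–body practices (yoga, Pilates, tai-chi, MBSR programs, etc". Section 2.6 defines the control condition as usual dance classes, "excluding mind–body practices (e.g., yoga, Pilates, tai-chi) that share overlap with the intervention". Under Section 2.4, intervention participants receive full disclosure of the programme and "provide additional written informed consent confirming understanding of the intervention and commitment to attending the sessions". Section 2.6 defines their arm by the sessions: "The intervention group will consist of participants who attend 12 weekly sessions (90–100 min each) structured across three phases". Neither place mentions outside mind-body practice for them.

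On measurement, Table 1 and Section 3.7 describe the same five outcome scales in both arms (SWLS, DASS-21, MAAS, SHS, LIS). Attendance and fidelity checklists (Sections 3.1 and 3.5) concern the sessions. Journals and interviews are collected in the intervention arm only.

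**The concern.** Randomization balances what participants bring to the trial. It does not balance a rule that is applied to one arm afterwards. Here the rule concerns an exposure that, in the protocol's own words, shares theoretical overlap with the intervention's "embodied awareness components and could confound results".

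If some intervention participants start yoga or a mindfulness course during the 12 weeks while controls comply with their instruction, the Group × Time contrast compares the programme plus any self-chosen practice with dance under a restriction. Section 2.1 describes the comparator as continuing regular recreational dance without mindfulness or somatic-reflective components, and the Conclusions attribute benefit to the integrated programme over traditional instruction alone. That attribution is cleaner if outside practice is handled alike in both arms. Uptake in the intervention arm is plausible: that arm alone is told after randomization about the mindfulness content, and it then practises breath work and body scanning weekly. If such practice helps, the shift would favour the intervention, most obviously on MAAS and DASS-21.

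**Working it through.** **Step 1: the text, arm by arm.**

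| Stage | Control | Intervention |
|---|---|---|
| Entry (2.3, criterion 1) | current practice excluded | current practice excluded |
| After randomization (2.4) | written instruction to avoid it | disclosure, consent, commitment to attend |
| Arm definition (2.6) | restriction repeated | no restriction stated |
| Recording of outside practice | none described | none described |

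Because criterion 1 applies to both arms, the exposure at issue is new uptake after randomization, not existing practice. Section 2.4 offers later participation to people who have completed a conflicting mindfulness intervention, so some entrants may have practised recently.

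**Step 2: the stated design figure.** The point does not depend on the sample size, but the arm sizes set the scale. With d = 0.50, α = 0.05, power 0.80 and 2:1 allocation, a one-sided two-sample calculation gives 38 + 76 = 114, the stated figure. The two-sided version gives 48 + 96 = 144. That difference is a separate matter; only 38 and 76 are used below.

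**Step 3: size of a possible shift.** Inputs: p, the uptake in the intervention arm minus the uptake in controls, and e, the effect of outside practice in SD units. The document gives neither, so both are assumptions. Shift = p × e, in SD:

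| p | e = 0.2 | e = 0.3 | e = 0.5 |
|---|---|---|---|
| 5% | 0.010 | 0.015 | 0.025 |
| 10% | 0.020 | 0.030 | 0.050 |
| 20% | 0.040 | 0.060 | 0.100 |
| 30% | 0.060 | 0.090 | 0.150 |

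Against the planning effect: 0.01/0.50 = 2% to 0.15/0.50 = 30%.

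**Step 4: against the precision of the trial.** For a simple comparison of T2 scores, the standard error of the standardized difference is √(1/38 + 1/76) = 0.199. The shift is then 0.01/0.199 = 0.05 to 0.15/0.199 = 0.75 standard errors. With no true programme effect, the noncentral t gives a two-sided rejection rate of 0.050 to 0.116 at nominal 0.05, and 0.010 to 0.034 at the Bonferroni level of 0.01.

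**Step 5: which part is bias.** Write intervention uptake as s + r, where s is what would have happened anyway and r is prompted by the programme, and suppose controls comply fully. The contrast then carries (s + r) × e. If both arms were unrestricted, controls would also have uptake s, and the contrast would carry only r × e, a consequence of assignment. The component due purely to restricting one arm is s × e. The document allows no split between s and r, so the table is an upper bound on this narrower component.

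**The case against.** The case for leaving this alone has several parts.

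- *Criterion 1 already covers everyone.* It is shown to all candidates, and its reference to concurrent practice can be read as extending over the study period. That reading is possible. But screening and the screening log operate at entry, and the protocol still gives controls a separate on-study instruction, with no counterpart for the other arm.
- *Controls choose their own classes, so their condition needs a written boundary, whereas a manual fixes the intervention content.* This explains why the control instruction exists. It does not explain why what intervention participants do outside class goes unmentioned.
- *The article is condensed.* Supplementary Files S1–S8, the consent form and the full case report forms are not shown, and any of them might hold a matching instruction or an outside-practice item. This stands. A reader might infer that the intervention arm is free to take up such practices, or that the imbalance could never be detected afterwards. Both inferences rest on silence in an article, and the documents do not establish either. What they do establish is that the rule, where it is written down, is assigned to one arm in two places.
- *Uptake prompted by the programme is part of the effect of being assigned to it* under the intention-to-treat principle in Section 2.4. This also stands, and it narrows the bias to the suppression of spontaneous uptake among controls.
- *Nothing in the document supports any particular uptake or effect.* Correct. An effect of 0.5 SD would credit outside practice, on top of the programme, with as much as the trial plans for the whole programme. A reader might infer that a material inflation has been shown; it has not.

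**Conclusion.** The asymmetry is clear in the text of Sections 2.4 and 2.6, and it concerns an exposure that Section 2.3 names as a potential confounder. Whether it produces a material bias is unknown. Under the assumed ranges (uptake difference 5–30%, effect 0.2–0.5 SD, a beneficial effect of outside practice) the contrast shifts by 0.01–0.15 SD towards the intervention. The low end is negligible; the high end would raise the false-positive rate at nominal 0.05 to about 0.12. Some of any shift may legitimately belong to the intention-to-treat effect. Confidence is high about the wording and low about the size. This is an inexpensive improvement to the design, not a flaw that undermines the trial.

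**What to change.** Give every participant the same written instruction on outside mind-body practice at the T0 visit, before randomization, and replace the control-only wording in Sections 2.4 and 2.6 with a statement that applies to both arms. If a supplementary file already contains a matching instruction, bring those two sections into line with it.

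Add one item at T2 in both arms asking whether the participant did any outside mind-body practice during the 12 weeks and how often. Report uptake by arm alongside the main results and leave the intention-to-treat analysis as it is.

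The cost is one sentence, one questionnaire item, and a 12-week request to intervention participants that controls already receive. The instruction need not reveal the mindfulness content beyond what the eligibility sheet already lists. If enrolment has closed, the T2 item alone would still make any difference between arms visible, provided T2 assessment is not complete.

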## 2. Experimental Design

### 2.1. Trial Design

This study has been prospectively registered on ClinicalTrials.gov (NCT07262177; brief title: Dance-Mindfulness Intervention for Well-Being in Recreational Adults-DanceMind) and approved by the institutional Research Ethics Committee (IEC, DPESS, UTH 4-2/2.4.2025; Supplementary File S8 [27]). The protocol follows SPIRIT [28,29], TIDieR [30], and CONSORT standards [31].

This is a two-parallel group randomized controlled trial (RCT). The intervention group receives a 12-week integrated dance-mindfulness protocol grounded in polyvagal theory, motor learning science, and embodied phenomenology. The control group continues regular recreational dance activities without mindfulness or somatic-reflective components. Participants are randomly allocated 2:1 (intervention: control) using computer-generated randomization with allocation concealment.

Quantitative assessments occur at baseline (T0) and post-intervention (T2 Week 12). Qualitative data collection occurs at mid-intervention (T1 Week 8) and post-intervention (T2 Week 12). This mixed-methods design permits concurrent testing of quantitative psychological outcomes (life satisfaction, subjective happiness, psychological distress, mindful attention, leisure involvement) and qualitative embodied experiences (somatic awareness, nervous system resilience, technical confidence, creative expression, relational belonging, meaning-making).

All procedures follow ethical principles outlined in the Declaration of Helsinki. Written informed consent is obtained prior to enrollment. Participants have the right to withdraw at any time without consequence. Personal data are stored securely in encrypted databases. Each participant receives a unique study code; identifying information is separated from research data. All facilitators hold CPR/First Aid certification and mindfulness training. Session checklists document adverse events. If a participant reports intense psychological distress, the study is suspended for that individual with clinical referral provided. Facilitators are trained to recognize signs of emotional dysregulation and provide immediate basic containment (quiet space, grounding breath), without attempting psychological exploration. Control group participants receive delayed access to the intervention after post-intervention assessment (Supplementary Files S1–S8 [27]).

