Site coordinators maintain a screening log documenting all preliminary screening contacts, including date of screening, recruitment source, preliminary eligibility status (age, dance experience, attendance availability, language fluency), exclusion criteria met (if applicable, specifying which criterion 1–6), clearance documentation status, and disposition (enrolled in baseline assessment, not meeting criteria, awaiting clearance). This log enables complete CONSORT [31] flowchart documentation and allows identification of potential selection bias or recruitment barriers. In the event that randomized participants withdraw or fail to meet attendance criteria (≤70% of sessions), they are retained in all analyses using intention-to-treat methodology. Missing outcome data will be addressed through multiple imputation or last-observation-carried-forward approaches, as appropriate based on data missingness patterns. Replacement participants are not recruited mid-trial, as this would create methodological complications (unbalanced final sample size, potential confounding from replacement timing differences). Final sample size analyzed may differ from target sample size and will be fully documented in the CONSORT compliant participant flowchart, which will be generated upon study completion detailing actual enrollment, randomization, and attrition data by group and reason for withdrawal.

All participants provide written informed consent prior to baseline enrollment. Personal data are handled in strict compliance with the General Data Protection Regulation. All participant identifiers are replaced with unique numeric codes; codebooks linking codes to identifying information are encrypted and stored separately from all research data, accessible only to the principal investigator. Paper materials are stored in locked filing cabinets in restricted-access laboratory space; digital data are stored on secure, password-protected institutional servers with automated daily backups. Data are retained for five years following study completion; paper documents are shredded, and digital data securely deleted thereafter, in accordance with institutional policies and GDPR regulations.

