### 3.2. Data Collection

Quantitative outcome measures (described in Section 2.5) are administered on paper at baseline (T0) and post-intervention (T2, Week 12). Post-intervention assessments are conducted by trained coordinators/assessors blinded to group allocation; blinding is maintained by: (1) providing assessors only the participant study code (no group information); (2) restricting assessor access to baseline data or randomization records; and (3) ensuring assessors have no knowledge of intervention attendance or session fidelity ratings. Completed questionnaires are entered into a secure electronic with double-entry verification. Missing data patterns are examined; Section 2.7 specifies handling strategies.

Weekly Journaling (Intervention Group Only): Intervention group participants complete standardized written reflections (5–10 min) at the end of each session using prompts addressing: breath/embodiment, emotional states, movement awareness, meaning-making, and perceived changes across weeks (prompts detailed in Supplementary File S3 [27]). Journal forms are collected weekly by facilitators and maintained in secure storage. A purposive sample of journal entries (selected from Weeks 1, 4, 8, and 12, plus entries with maximum phenomenological variation) is analyzed for thematic patterns regarding embodied experience, affective change, and perceived transformation using Reflexive Thematic Analysis with phase-specific coding (Weeks 1–4, 5–8, 9–12; detailed methodology in Supplementary File S3 [27]). Two independent coders will analyze qualitative data using structured coding protocols; differences are resolved through consensus discussion. Control group participants do not complete journaling; they complete quantitative assessments only (T0 and T2).

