### 3.7. Post-Intervention Assessment (T2, Week 12)

At Week 12, all randomized participants complete the final assessment to evaluate intervention outcomes and longitudinal progression. Both intervention and control groups complete the identical battery of five outcome measures administered at baseline (T0), following standard administration procedures to ensure comparability. The same subsample of participants interviewed at T1 completes a second semi-structured interview (20–30 min). The T2 guide (Supplementary File S3) [27] retains the core phenomenological domains but pivots the inquiry toward integration and transformation. Participants reflect on their trajectory across the full 12-week period, enabling an analysis that compares T1 (midpoint) and T2 (endpoint) narratives to map the developmental arc from early somatic grounding to late-phase creative expression.

Intervention participants complete a final journal entry (Supplementary File S3) [27] specifically designed to export a retrospective comparison between their Week 1 and Week 12 embodied states. This completes the qualitative dataset, which is then stratified into three Phase-aligned segments (Weeks 1–4, 5–8, 9–12) for Reflexive Thematic Analysis (coding framework detailed in Supplementary File S3 [27]).

The qualitative strategy at T2 focuses on triangulation: phase-specific journal themes are cross-referenced with longitudinal interview narratives to construct a mechanistic explanation of embodied change. Control group participants complete only the quantitative assessment, preserving the distinction between outcome evaluation (quantitative/comparative) and process evaluation (qualitative/descriptive).

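### With questionnaires at T0 and T2 only, the permitted last-observation-carried-forward option is baseline carried forward: it sets change to zero for anyone missing T2 and can bias the arm contrast

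*Protocol article*

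**What the plan says.** The only missing-data rule in the article is in Section 2.4: "Missing outcome data will be addressed through multiple imputation or last-observation-carried-forward approaches, as appropriate based on data missingness patterns". The same paragraph says of participants who withdraw or attend too few sessions that "they are retained in all analyses using intention-to-treat methodology".

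The measurement schedule is in Section 2.1: "Quantitative assessments occur at baseline (T0) and post-intervention (T2 Week 12". The Week 8 visit gives no questionnaire score: "Qualitative data collection occurs at mid-intervention (T1 Week 8) and post-intervention (T2 Week 12". Section 3.2 says of controls that "they complete quantitative assessments only (T0 and T2". Table 1 lists T0 and T2 for all five scales.

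Section 3.2 sends the reader elsewhere for the rule: "Missing data patterns are examined; Section 2.7 specifies handling strategies". Section 2.7 covers normality checks, ANOVA, MANOVA, ANCOVA, non-parametric tests and correlations. It contains no missing-data rule.

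On who is assessed at the end, Section 3.7 states: "At Week 12, all randomized participants complete the final assessment to evaluate intervention outcomes and longitudinal progression". On distress, Section 2.1 states: "If a participant reports intense psychological distress, the study is suspended for that individual with clinical referral provided".

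**The concern.** Carrying forward the last observation needs an intermediate value to have any content. Here there is none, so the method fixes T2 equal to T0 for anyone without a T2 score. The main test in Section 2.7 is a 2 × 2 Group × Time analysis, whose interaction is the difference between arms in T0–T2 change. Because all randomized participants are kept in the analysis, the imputed zeros go straight into that contrast.

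Three things are at stake:

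- The effect estimate can be diluted, or shifted in either direction when missingness is unequal and both arms change.
- The imputed zeros are treated as observed data, so the uncertainty about the missing values is ignored.
- The choice between two methods that can give different answers is made after the missingness has been seen, with no criterion, for five primary outcomes.

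**Working it through.** The plan has no figure of its own on this point. It states no dropout rate and no expected change in either arm.

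**Inputs from the article.** 76 intervention and 38 control participants, and an effect of 0.50 SD (Section 2.4). Two questionnaire occasions (Sections 2.1, 2.5 and 3.2, and Table 1). A contrast of change between arms (Section 2.7).

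**Assumptions.** Missing-T2 proportions dI (intervention) and dC (control) between 5% and 30%. Missingness unrelated to change. T0–T2 correlation 0.6 for the simulated error rates. Scores oriented so that higher is better.

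**Formula.** Let μI and μC be the true mean changes in SD units. Carrying baseline forward replaces a fraction dI or dC of the changes by zero, so the expected contrast is

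(1 − dI) × μI − (1 − dC) × μC, instead of μI − μC.

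**Case 1, effect in the intervention arm only (μI = 0.5, μC = 0).** The control term is zero, so only dI matters.
- dI = 10%: 0.90 × 0.5 = 0.45
- dI = 20%: 0.80 × 0.5 = 0.40
- dI = 30%: 0.70 × 0.5 = 0.35

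At 20%/10% missing, simulated power at two-sided 0.05 is about 0.66, against about 0.73 for complete cases.

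**Case 2, no effect but a common change μ in both arms.** The formula reduces to (dC − dI) × μ.
- 20%/10%, μ = +0.4: (0.10 − 0.20) × 0.4 = −0.04 SD
- 30%/5%, μ = +0.4: (0.05 − 0.30) × 0.4 = −0.10 SD
- 30%/5%, μ = −0.4: (0.05 − 0.30) × (−0.4) = +0.10 SD
- 15%/15%, any μ: 0

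**Simulated type I error in Case 2** (two-sided 5%, pooled-variance t-test on change, 76:38):

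| Missing (intervention/control) | Common change | False contrast | Rejection |
|---|---|---|---|
| 20%/10% | +0.4 SD | −0.04 | about 6–7% |
| 30%/5% | +0.4 SD | −0.10 | about 11% |
| 30%/5% | −0.4 SD | +0.10 | about 11% |
| 15%/15% | +0.4 SD | 0 | about 5% |

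Complete-case rejection in the unequal-missingness scenarios stays at about 5%.

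Part of the 11% is not bias. Filling in zeros makes the variances unequal, and the pooled test is sensitive to that under 2:1 allocation. With no common change at 30%/5% there is no bias, yet the pooled test rejects about 6.5%. With the 0.4 SD change, a Welch test rejects about 9%.

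The baseline-adjusted ANCOVA in Section 2.7 does not remove the problem. It gives 0.40 when the effect is 0.5 SD in the intervention arm only with 20%/10% missing, and type I error of about 11–12% in the 30%/5% scenarios.

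**The case against.** **Carry-forward is only an option.** Multiple imputation is named first. This is correct, so the point concerns a permitted method, not a mandated one. A reader might infer that every dropout is recorded as unchanged. The documents do not support that: people who stop attending are to be kept in the analysis, and Section 3.7 has all randomized participants assessed at T2. Only a missing T2 score would be imputed.

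**The larger error rate needs an extreme split.** The 11% figure rests on an assumed 30% versus 5%. At 20% versus 10% it is about 6–7%, and with equal missingness about 5%. This stands.

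**The likely direction is conservative.** If both arms improve and the intervention arm loses more people, the bias runs against the intervention. In the 30%/5% case with both arms improving, false claims of benefit fall to about 0.6%, against a nominal 2.5%. A false benefit needs both arms to worsen with more loss in the intervention arm, or both to improve with more loss among controls. The article does not predict either pattern.

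**Greater loss in the intervention arm is not established.** A second consent and weekly 90–100 min sessions might raise it. The 48-hour contact after a missed session, make-up sessions and barrier support (Section 3.5) might lower it.

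**Hidden deterioration.** A reader might infer that distressed participants lose their T2 assessment and that worsening on DASS-21, taken as the main safety signal, is then recorded as no change. No passage gives DASS-21 that role; safety is tracked by session checklists and incident reports. No passage says that suspension ends assessment. Section 1.2 pauses participation in that session, Section 2.1 suspends the study for the individual, and Section 3.1 says participation may be suspended. The wording needs reconciling, but it does not show that deterioration would be hidden.

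**Details may sit in an analysis plan.** The imputation model may. The carry-forward option itself is stated in the article.

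**Conclusion.** The concern holds as a defect in a stated method. With two questionnaire occasions, the carry-forward option can only enter zero change for anyone missing T2, and the choice to use it is left until missingness has been seen.

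If it is used, the most direct consequence is dilution of an effect confined to the intervention arm: 0.50 to 0.40 SD at an assumed 20% missing. With unequal missingness and a common change of 0.4 SD, the false contrast is about 0.04 SD (20%/10%) to 0.10 SD (30%/5%), in either direction.

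All these sizes rest on assumed dropout, assumed change and missingness unrelated to change. There is no bias if those missing T2 truly had no mean change, or if there is no effect and both missingness and change are equal across arms. Neither condition is a reason to keep the option, since Section 4 of the article expects the intervention arm to improve more than controls.

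**What to change.** 1. In Section 2.4, delete the carry-forward option. Name multiple imputation as the single primary method, using arm, the T0 scores of all five scales and baseline covariates available in both arms, and feeding the baseline-adjusted comparison. Leave session attendance out of the imputation model: the article describes recording it only at intervention sessions, so it could not be used for controls.
2. Add a delta-adjusted sensitivity analysis for data missing not at random.
3. Correct the cross-reference in Section 3.2, or move the rule into Section 2.7.
4. State that T2 questionnaires are sought from all randomized participants who have not withdrawn consent, whatever their session attendance. This agrees with Section 3.7 and respects the right to withdraw in Section 2.1.
5. Reconcile Sections 1.2, 2.1 and 3.1 on what is suspended after distress, so that it is clear whether T2 assessment continues.

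The cost is wording and slightly wider intervals. The change should be made before outcome data are examined.
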